## Abstract

**Background:**

Sleep is essential for normal and healthy living. Lack of good quality sleep affects physical, mental and emotional functions. Currently, the treatments of obesity-related sleep disorders focus more on suppressing sleep-related symptoms pharmaceutically and are often accompanied by side effects. Thus, there is urgent need for alternative ways to combat chronic sleep disorders. This study will investigate underlying mechanisms of the effects of exercise and diet intervention on obesity-related sleep disorders, the role of gut microbiota in relation to poor quality of sleep and day-time sleepiness, as well as the levels of hormones responsible for sleep-wake cycle regulation.

**Methods/design:**

Participants consist of 330 (target sample) Finnish men aged 30 to 65 years. Among them, we attempt to randomize 180 (target sample) with sleep disorders into exercise and diet intervention. After screening and physician examination, 101 men with sleep disorders are included and are randomly assigned into three groups: exercise (n = 33), diet (n = 35), and control (n = 33). In addition, we attempt to recruit a target number of 150 healthy men without sleep disorders as the reference group. The exercise group undergoes a six-month individualized progressive aerobic exercise program based on initial fitness level. The diet group follows a six month specific individualized diet program. The control group and reference group are asked to maintain their normal activity and diet during intervention. Measurements are taken before and after the intervention. Primary outcomes include objective sleep measurements by polysomnography and a home-based non-contact sleep monitoring system, and subjective sleep evaluation by questionnaires. Secondary outcome measures include anthropometry, body composition, fitness, sleep disorder-related lifestyle risk factors, composition of gut microbiota and adipose tissue metabolism, as well as specific hormone and neurotranmitter levels and inflammatory biomarkers from venous blood samples.

**Discussion:**

It is expected that the improvement of sleep quality after exercise and diet intervention will be evident both in subjective and objective measures of quality of sleep. Additionally, the change of sleep quality induced by exercise and diet intervention is expected to be related to the changes in specific hormones and inflammatory biomarkers, and in the composition of gut microbiota.

**Trial registration:**

Current Controlled Trials ISRCTN77172005

## Background

We spend one-third of our lifetime in sleep. Sleep is absolutely essential for maintaining healthy physical, mental and emotional functions. Sleep disorder impairs one’s ability to think quickly, to work efficiently, and to associate freely, thus making one feel generally ’disconnected’ from the world. In some serious cases, the sleep disorder-related conditions may lead to serious neurasthenia and depression [1,2]. Obesity is a major risk factor for sleep disorders, which may cause symptoms such as obstructive sleep apnea (OSA) [3,4]. OSA has an estimated prevalence of 2% to 4% among adults aged 30 to 60 years and the proportion is increasing [5,6]. OSA is associated with significant morbidity and mortality due to accidents, cardiovascular diseases, and stroke [7,8]. In addition, insomnia is a common sleep disorder that impairs quality of life from both physiological and psychological aspects, with prevalence range from 10% to 40% in Western countries [9-11]. Besides insomnia, a considerable proportion of the general adult population reports chronic mild to moderate sleep complaints which result in long-term poor quality of sleep, as well as increased health care visits [12].

Two thirds of middle-aged sleep apneic men are obese, and visceral obesity has been observed to be a primary risk factor for OSA [7]. Obesity reflected by body weight and body mass index (BMI) is also related to poor subjective quality of sleep [13] and short sleep duration [14-18] among adults. A widely supported theory that obesity induces inflammatory reactions may explain the association between obesity and sleep disorders [19,20]. Elevated levels of inflammatory biomarkers, such as C-reactive protein (CRP) [21,22], interleukin-6 (IL-6) [22,23], and tumor necrosis factor-alpha (TNF-alpha) [24] are reported among OSA patients. People with non-apneic sleep disorders also demonstrate changed levels of inflammatory biomarkers [25-27]. Both short or excessive habitual sleep duration are linked with greater levels of CRP [25-27], while short sleep duration recoded by polysomnography (PSG) is related to higher levels of TNF-alpha [25]. However, it is still unclear whether inflammation causes sleep disorders or vice versa [28-31].

Sleep disorders elevate the risk of obesity by affecting eating patterns and other lifestyle factors. Short sleep duration is associated with higher energy intake, mostly due to increased consumption of saturated fat [32]. Weight loss from three months exercise training or one year diet control alleviates the symptom of OSA by lowering the apnea-hypopnea index (AHI) [33-35]. The possible association between weight loss and subjective quality and quantity of sleep is exhibited in some adult women [36]. Despite the change of body weight and BMI, lifestyle intervention through aerobic or resistance exercise may improve quality of sleep in middle-aged and older adults with sleep complaints [9,12]. However, more clinical trials are needed since very few previous studies have utilized objective sleep measurements [32,37].

Gut microbiota is suggested to act as an important factor regulating adipose metabolism, and affecting neurological functions. Animal studies show that gut microbiota affects energy harvest from diet and energy storage in the host. The association is reflected by lower metabolic rate, increased hepatic production of triglycerides, and promoted storage of triglycerides in adipocytes among mice with gut microbiota compared with their germ-free counterparts [38]. In human studies, composition of gut microbiota shows differences between obese and lean subjects [39], and certain types of gut microbiota may independently link to obesity-related metabolic disorder [40]. Moreover, gut microbiota may be involved in modulation of both central and peripheral nerve function, such as the hypothalamus-pituitary-adrenal (HPA) axis and thus associate with neuropsychiatric conditions including anxiety, depression, and sleep disorders [41,42]. Composition of gut microbiota can be altered through long-term dietary intervention [43]; however whether changing the human intestinal microbiota through lifestyle intervention helps to mediate sleep disorders has yet to be studied.

### Methods/design

The study aims to involve 330 Finnish men aged 30 to 65 years with or without sleep disorders. Participants are recruited from City of Jyväskylä health care centers in the Central Finland Health Care District and its surroundings via doctors’ referral and advertising in news media and on the internet between 28 April 2011 and 2 April 2013. Among the total 330 target number of participants, 180 are sleep disordered with OSA or insomnia (OSA is diagnosed and referred by a sleep specialist physician at the Central Hospital of Central Finland prior to the baseline assessments. Insomnia is reported first by the participants then examined by a physician prior to other baseline assessments. The definition of insomnia is based on the following symptoms: recurrent difficulty in falling asleep, too short sleep duration or poor quality of sleep during the previous three months [44]). The remaining 150 participants are healthy men without sleep disorders.

Among the 180 men with sleep disorders, 171 responded to the initial advertisement (response rate: 95%). A screening interview was carried out for interested participants who contacted the researchers. The screening covered the participant’s health and medical conditions and certain lifestyle factors such as physical activity, type of employment, and so on. Sixty-six participants did not meet the inclusion criteria. The remaining 105 participants were invited to the laboratory and evaluated by a physician to make sure that they could be included in the intervention study. The examination by a physician included cardiac and musculoskeletal status evaluations, risk evaluation concerning exercise tolerance [45], and family background-related diseases, through which four participants were excluded. Thereafter, baseline tests were performed. Participants with sleep disorders were randomized into three groups: exercise, diet, and control. The exercise and diet groups followed a six-month guided individualized exercise and diet counseling intervention program respectively, while the control group and reference group members were asked to maintain their current life habits. Measurements were carried out before and after intervention, and in addition, some variables were also measured at the three-month time point.

A target number of 150 healthy participants have been continuously recruited. All healthy participants in the initial contact have to pass the same evaluations as their sleep disordered counterparts. After the baseline assessments, a subgroup of the healthy participants are asked to participate in the same extensive sleep measurements and follow-up tests as the apnea group in order to serve as a reference group (target n = 12).

The trial is registered under http://www.controlled-trials.com: ISRCTN77172005. A summary of the study design is presented in Figure 1.

**Figure 1 F1:**
[figure not shown]
**Flow diagram of the study design. (A) **study design summary of objectives 1 and 2; **(B)** study design summary of objectives 3 to 5.

### Hypotheses

    1. Physical activity is beneficial in terms of good quality and proper duration of sleep. The levels of melatonin, cortisol, and neuro-active steroids are modified by physical activity and thereby influence sleep.

2. The amount of micronutrients in the diet, such as tryptophan and the vitamin Bs, are correlated with quality and duration of sleep.

3. Six-month guided individualized exercise or diet counseling intervention can independently alleviate sleep disorders among adult men with sleep disorders. The improvement can be observed by changes in duration of total sleep, duration and proportion of slow-wave sleep (SWS) and rapid eye movement (REM) sleep, stress reactions based on heart rate variability (HRV) and AHI (participants with OSA), as well as subjective sleep measures such as the Epworth Sleepiness Scale score.

4. Prolonged good quality of sleep after six-month individualized exercise intervention is linked to decreased oxidative stress that in turn may affect melatonin levels in the peripheral circulation because indole is rapidly used to combat free radical damage. Exercise also affects cortisol and neuro-active steroid levels. The mutual interactions between exercise and these hormonal milieus are responsible for sleep-wake cycle regulation.

5. Six-month guided individualized exercise and diet counseling intervention can improve sleep quality through modification of gut microbiota composition. The composition of the gut microbial community is host-specific, evolving throughout an individual’s lifetime and susceptible to both exogenous and endogenous modifications. Hence, the cross-talk between gut hormones and hypothalamic factors (gut-brain axis) is important in the regulation of food intake and sleep disorders.

### Primary and secondary outcomes

#### Primary endpoints

Duration and proportion of sleep stages, heart rate, heart rate variability, respiration and body movements during sleep, and AHI (PSG for participants with OSA;pressure sensor measurement for both OSA and other participants)

Subjective measures of duration and quality of sleep (Nordic sleep disorder questionnaire, Epworth Sleepiness Scale, seven-day sleep diary)

Lifestyle risk clusters related to sleep disorders (healthy versus sleep disordered patients)

#### Secondary endpoints

Anthropometry (body weight and height; waist, hip, chest and neck circumferences)

Blood pressure

Body composition (dual-energy x-ray absorptiometry and bioimpedance)

Fitness (2 km walking test, three-minute step test)

Composition of gut microbes (fecal sample)

Subcutaneous adipose tissue metabolism (total RNA)

Venous blood samples (total cholesterol, HDL-cholesterol, LDL-cholesterol, triglycerides, glucose, insulin, histamine, tryptophan, melatonin, cortisol, adrenalin, leptin, adiponectin, neuro-active steroids, fatty acids, B vitamins, fatty acid profile, and inflammatory variables such as CRP, IL-6, TNF-alpha, and so on)

### Participants

Participants in this study consist of a target sample of 330 Finnish men aged 30 to 65 years.

Participants with sleep disorders: a target number of 180 men with sleep disorders are to be randomized into exercise or diet intervention groups. After screening and physician examination, 35 men with diagnosed mild to moderate OSA and 66 with insomnia confirmed by a physician have been included.

Inclusion criteria for apnea and insomnia patient groups:

• Men in an age range of 30 to 65 years

• Occasionally physically active or sedentary (regular leisure-time exercise ≤ two times per week and ≤ 45 minutes per session)

• Report recurrent difficulty in falling asleep, too short sleep duration or poor quality of sleep during past two months, or with mild to moderate OSA (AHI 5 to 30/hour) with or without continuous positive airway pressure (CPAP) treatment. If under treatment, nasal CPAP for a minimum period of six months prior to the baseline measurements, with a minimum adherence to CPAP therapy for four hours per night

• Relatively healthy (free from cardiovascular comorbidities)

Exclusion criteria:

• Diseases and medications related to: insulin dependent diabetes mellitus, Crohn’s disease, sarcoidosis, celiac disease, thyroid, liver and severe heart diseases, chronic diarrhea, ulcerative colitis, rheumatoid arthritis, severe osteoarthritis, systemic lupus erythematosus, and cancer during the past three years

• Currently taking a special diet (such as a very low calorie diet)

• Other diagnosed sleep disorders (such as narcolepsy)

• Shift workers (working during the night)

• Reported cognitive impairment

• Using antibiotics during the previous three months

• History of eating disorders

• Participants using CPAP, professional drivers and other professions that are at risk of accidents due to discontinuation in CPAP treatment

• Not suitable for the study by a physician’s evaluation

Healthy participants: a target number of 150 healthy men without sleep disorders are intended to be recruited as the reference group. Sixty-three overweight/obese (BMI from >25 to <38) and 44 normal body weight (BMI <25) men with no diseases and taking no medications have been included so far.

Inclusion criteria for reference (healthy men) group:

• Men in an age range of 30 to 65 years

• No chronic sleep disorders and taking no medications related to sleep disorders

• No disease and medications during past one year

• Relatively healthy (free from cardiovascular comorbidities)

Exclusion criteria for reference (healthy men) group are the same as for the patient group.

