## Discussion

Currently there is a lack of evidence regarding the associations between lifestyle, metabolism, and sleep. This study focuses on middle-aged men with two different sleep disorders; OSA and insomnia. Through a six-month intervention with either aerobic exercise or optimized diet, results from a range of sleep assessments will provide a clear information about differences in sleep duration, sleep stages, and quality of sleep among the different groups. A comparison between subjective sleep evaluation and objective sleep measurement results among sleep disordered men will also be possible with the data from this study. Variables in the physiological dimension are important references for explaining mechanisms behind sleep and lifestyle. Measurements of neurotransmitters, gut microbiota composition, and adipose tissue characteristics before and after intervention in this trial may strengthen evidence for links between lipid metabolism and sleep outcomes, or find new associations in related fields.

Comparing the participants who have sleep disorders to their healthy counterparts will allow us to find out which lifestyle risk factors are associated with sleep quality and duration. The detailed information collected in this study regarding levels of physical activity and different composition of food intakes and micronutrients will be used to test our hypotheses 1 and 2. This information can be used for diagnosing risk factors and developing healthcare guidance related to sleep disorders.

In this study we applied modern technology combined with socio-psychological support and self-commitment to ensure the participants’ compliance during the intervention. The online exercise diary service and remote food analysis and counseling have been rarely, if ever, used in previous studies and thus may enhance the efficacy and reliability of the intervention. We believe that allowing participants to monitor their progress more effectively could be a potent tool in helping them to change inactive and unhealthy lifestyles.

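### Low leisure exercise is an entry condition for patients but not for reference men, so the activity part of the healthy-versus-patient lifestyle endpoint is biased by design

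*Protocol article*

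**What the plan says.** For the apnea and insomnia groups, the Participants section lists as an inclusion criterion "Occasionally physically active or sedentary (regular leisure-time exercise ≤ two times per week and ≤ 45 minutes per session".

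The same section has a separate list headed "Inclusion criteria for reference (healthy men) group". It covers age 30 to 65, "No chronic sleep disorders and taking no medications related to sleep disorders", no disease or medication in the past year, and "Relatively healthy (free from cardiovascular comorbidities". The age and cardiovascular items repeat those for patients; the activity item does not appear. The section then states that "Exclusion criteria for reference (healthy men) group are the same as for the patient group", and that exclusion list has no activity item.

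Under Primary endpoints the article lists "Lifestyle risk clusters related to sleep disorders (healthy versus sleep disordered patients". The Discussion says "Comparing the participants who have sleep disorders to their healthy counterparts will allow us to find out which lifestyle risk factors" are associated with sleep, and that the recorded activity levels will serve to test hypotheses 1 and 2. Hypothesis 1 begins: "Physical activity is beneficial in terms of good quality and proper duration of sleep".

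**The concern.** Activity is an exposure in the healthy-versus-patient comparison, and eligibility cuts off its upper range in one of the two groups only. Any reference man who exercises more than the limit has no possible counterpart among the patients. The group difference in leisure activity therefore partly reflects the entry rule, and it points in the direction that hypothesis 1 predicts. The Discussion intends the results for identifying risk factors and developing healthcare guidance, so an eligibility rule could be reported as a risk factor. Covariate adjustment cannot restore the active patients who were never admitted.

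**Working it through.** The article gives no power or error-rate figure for this comparison, so there is nothing to reproduce beyond the counts.

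**Inputs from the Participants section**
- Patients: 35 with apnea + 66 with insomnia = 101.
- Reference men so far: 63 + 44 = 107 (target 150).

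**Assumptions, not in the article**
- The share q of reference men above the patients' limit, varied from 1% to 50%.
- A two-sided test at 0.05.
- No true link: both groups come from one activity distribution, normal on a suitable scale, and patients are truncated at its (1 − q) quantile c.

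**Spurious difference.** With φ the standard normal density, in SD units:
- shift δ = φ(c)/(1 − q)
- variance among patients v = 1 − cδ − δ²

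**Worked case, q = 20%**
- c = 0.842 and φ(c) = 0.280, so δ = 0.280/0.80 = 0.350.
- v = 1 − 0.842 × 0.350 − 0.350² = 0.583.
- Standard error = √(1/107 + 0.583/101) = 0.123, so δ/SE = 2.85.
- Chance of p < 0.05 ≈ Φ(2.85 − 1.96) = 0.81. Simulation of the Welch test (4,000 runs) gives 82%.

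**Range of q, 101 versus 107 men.** The last column tests the proportion above the limit: 0/101 against a binomial count out of 107. Fisher's exact test is significant from 6 such men.

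| Share q above limit | Spurious shift (SD) | False positive, mean activity (Welch) | False positive, proportion above limit (Fisher) |
|---|---|---|---|
| 1% | 0.03 | 6% | 0.1% |
| 5% | 0.11 | 13% | 45% |
| 10% | 0.20 | 34% | 96% |
| 20% | 0.35 | 82% | about 100% |
| 30% | 0.50 | 99% | about 100% |
| 40% | 0.64 | about 100% | about 100% |
| 50% | 0.80 | about 100% | about 100% |

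With the target of 150 reference men, the Welch rates at 5%, 10% and 20% are 14%, 38% and 88%.

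**Second model.** Take weekly sessions as Poisson with mean 2.0 in everyone, and patients truncated at two or fewer.
- Patients' mean is 1.20 and variance 0.56, against 2.00 and 2.00 in reference men.
- d = 0.80/√((2.00 + 0.56)/2) = 0.71.
- z = 0.80/√(2.00/107 + 0.56/101) = 5.1.
- Means of 1.5 to 3.0 give z of 3.3 to 8.8. These means imply that 19% to 58% of men exceed two sessions, so this model does not cover small shares.

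**With the same limit in both groups.** The Welch rejection rate returns to nominal: 5.3% at q = 20% and 4.8% at q = 40%, with 101 versus 107 men.

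**The case against.** The Methods/design section says healthy men must pass the same evaluations as the sleep-disordered men, and the screening interview described there asks about physical activity. One could read this as applying the same limit. That reading is possible but weaker. An evaluation is not a cut-off; the sleep criteria for the two groups are opposite, so identical criteria cannot be meant; and the group's explicit list omits the item. If the limit was applied, the list needs correcting.

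Several limits on the point do stand:

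- **Measure.** The entry limit concerns regular leisure exercise. Under Study examinations, activity is recorded by type and duration for all physical activity, up to seven days. Truncating one component shifts the total by less than the table shows.
- **Reach.** Diet also enters the lifestyle comparison and is not truncated. Hypothesis 1 can be tested within groups, where this mismatch causes no bias, although the activity range among patients is narrow.
- **Analysis plan.** The SAP is not shown and might restrict the groups. The asymmetry, however, lies in the eligibility criteria, which the article states in full for both groups.

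Two stronger readings are tempting. A reader might infer that a false finding is close to certain. The article does not support that, because it does not give the share above the limit, and at 1% to 5% the Welch rate is only 6% to 13%. A reader might also infer that body composition must differ between the groups whatever the truth. Nothing in the article establishes that, and the BMI mix of the reference men (63 overweight or obese, 44 normal weight) bears on it as well.

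**Conclusion.** The point holds for the activity component of the healthy-versus-patient lifestyle endpoint. As the criteria are written, that contrast is biased towards less active patients whenever any reference men exceed the limit. The direction is fixed, but the size is not known. With no true link and 101 versus 107 men, a false difference in mean leisure activity becomes more likely than not somewhere between a 10% and a 20% share above the limit, and near certain from about 30%. These figures rest on the normal model, the assumed share, and leisure activity itself being the analysed variable. Fitness is a likely correlate and may be affected, but that was not calculated.

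The randomized exercise, diet and control comparisons are untouched, because all three arms entered under the same limit.

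**What to change.** State whether the limit was applied to reference men. If it was, add it to their inclusion criteria and the bias goes.

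If it was not, choose one of the following before the healthy-versus-patient analysis:

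1. In between-group analyses of physical activity, and of fitness as a likely correlate, include only reference men whose screening interview shows that they meet the patients' limit. Apply the filter to all reference men, so that men recruited earlier and later are treated alike.
2. Take activity out of the between-group clusters, and test the activity part of hypothesis 1 within patients and within reference men separately.

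Both use data already collected, provided the screening answers record frequency and session length. The first option loses reference men: of 107, about 86 remain if 20% exceed the limit (107 × 0.80) and about 64 if 40% do (107 × 0.60). It also confines the comparison to low exercisers, so it can say less about activity as a risk factor. The second gives up the between-group statement on activity, and the range among patients stays narrow.

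### The one-year disease- and medication-free rule binds only the healthy men, so the healthy-versus-patient comparison of lifestyle risk clusters is confounded, to an unknown degree, by conditions and medicines outside the shared exclusion list

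*Protocol article*

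**What the plan says.** All the entry criteria are in the protocol article under Participants.

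- **Reference men** must meet "No disease and medications during past one year". The overweight/obese and normal-weight men recruited to date are described as "men with no diseases and taking no medications have been included so far".
- **Patients** must be "Relatively healthy (free from cardiovascular comorbidities", and must not fall under an exclusion list that begins "Diseases and medications related to: insulin dependent diabetes mellitus, Crohn’s disease, sarcoidosis, celiac disease, thyroid, liver and severe heart diseases, chronic diarrhea" and goes on to further named conditions, recent antibiotic use, cognitive impairment, a history of eating disorders and a physician's judgement of unsuitability.
- **Both groups** share that list: "Exclusion criteria for reference (healthy men) group are the same as for the patient group". They also share the cardiovascular criterion. The one-year rule is therefore an extra condition on the reference men.

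Primary endpoints includes "Lifestyle risk clusters related to sleep disorders (healthy versus sleep disordered patients" (the parenthesis closes there). The Discussion says that comparing the two groups "will allow us to find out which lifestyle risk factors are associated with sleep quality and duration", and adds that the information can serve to diagnose risk factors and develop healthcare guidance.

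**The concern.** The healthy-versus-patient comparison is not randomised, so its meaning depends on how the two groups were selected. One group has been cleared of all disease and medication for a year. The other has been cleared only of named conditions. A man with, say, non-insulin-dependent diabetes or osteoarthritis short of severe is not barred by the list from entering as a patient, but the same man without a sleep disorder cannot enter the reference group.

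Diet and activity may well differ between men with and without such conditions or medicines. If so, part of the difference on a listed primary endpoint would come from the unequal health screen and be credited to sleep disorder. Hypotheses 1 and 2, which the Discussion ties to this information, and any guidance built on it would carry the same error.

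**Working it through.** **1. Criteria side by side**

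| Requirement | Patients | Reference men |
|---|---|---|
| Free of cardiovascular comorbidity | yes | yes |
| Clear of the listed diseases and related medicines | yes | yes |
| No disease or medication at all for one year | no | yes |
| Low leisure-time exercise | yes | not listed |

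The third row is the point at issue. Methods/design says that healthy men pass the same evaluations as patients. That is a shared screening procedure and does not give patients the one-year rule. The fourth row is a separate asymmetry, taken up under the fix.

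**2. Counts.** Patients: 35 with sleep apnoea + 66 with insomnia = 101. Reference men so far: 63 + 44 = 107. The article states no effect size, power or comorbidity rate for this comparison, so there is no figure of the plan's to reproduce.

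**3. Illustration on a continuous score (q and k are assumptions).** Let a share q of patients have a condition or medicine outside the list, let those men differ by k SD, and let sleep disorder have no true association.

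- Spurious difference = q × k. Low: 0.2 × 0.3 = 0.06 SD. High: 0.4 × 0.5 = 0.20 SD.
- Standard error = √(1/107 + 1/101) = 0.139 SD.
- Shift in the test statistic: 0.06/0.139 = 0.43; 0.20/0.139 = 1.44.
- Chance of rejecting at two-sided 5%: about 7% and about 30%.

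**4. Illustration on a binary factor (all inputs assumed).** Prevalence is p0 = 30% in disease- and medication-free men. In patients it is (1 − q)p0 + q·p1, where p1 follows from p0 and an odds ratio for other disease or medication. Two-proportion pooled z-test, two-sided 5%, 101 v 107 men, odds ratio 2:

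| q | Spurious odds ratio | Chance of rejecting |
|---|---|---|
| 10% | 1.08 | 5.7% |
| 30% | 1.25 | 11.6% |
| 50% | 1.43 | 23.3% |

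Over odds ratios 1.5 to 3 and q from 10% to 50%, the spurious odds ratio runs from 1.04 to 1.77 and the rejection rate from 5.2% to 50.3%. With the same rule in both groups, q = 0 and these return to 1.00 and 5%.

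**5. Can adjustment repair it?** No reference man has another disease or medicine, so the groups do not overlap on that factor. A single indicator for it in a linear model would be estimated among patients only. The adjusted difference would then be that between patients without other conditions and reference men, which is the restricted comparison under another name. Adjusting for other covariates does not reach the problem.

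**The case against.** The strongest reply has four parts.

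*It is an analysis-plan matter.* Covariates and sensitivity analyses for an observational comparison usually sit in the analysis plan, and this article has no analysis section. A reader might infer that the article commits to an unadjusted comparison. It does not: it names the endpoint and the groups and says nothing about adjustment. The point survives because the stated criteria create the imbalance and leave no overlap for an adjustment to work with.

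*Patients are well screened.* A reader might infer that the patients are in generally poor health. The documents do not support that, given the cardiovascular criterion, the long exclusion list and the physician's examination. Only conditions and medicines outside the list are at issue. This part stands and narrows the point.

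*The size is assumed.* This stands. Nothing in the article supports any particular share of affected patients or any effect on a lifestyle score, and at the low end 7% against a nominal 5% is trivial.

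*Restriction costs power and can mislead.* This also stands. At a 40% share about 61 patients remain, and power for a true difference of 0.4 SD (assumed, two-sided 5%) falls from about 82% to about 70%. A rule that a factor counts only if it is significant again would mistake lost power for confounding. A difference in physical activity could also pass such a check because of the patients-only exercise criterion.

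A strictly healthy reference group is a common and defensible choice. What needs care is the conclusion drawn from it.

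**Conclusion.** The point holds within limits. The one-year rule is one-sided in the current text and bears on a listed primary endpoint and on the risk-factor reading in the Discussion. The comparison is therefore confounded by conditions and medicines outside the exclusion list, in so far as patients have them and they go with lifestyle.

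The size is unknown. The 7–30% range and the wider 5.2–50.3% range show what follows from assumed inputs and are not estimates for this trial. The sponsor can settle the main unknown by counting the affected men among the 101 patients; if there are few, the effect is small.

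A reader might extend the concern to the exercise, diet and control contrasts. The documents do not support that: those arms were randomised from one patient population under one set of criteria.

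**What to change.** Keep enrolment and the full comparison as they are. Then:

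1. Pre-specify, before the healthy-versus-patient comparison is run, a repeat restricted to patients who also meet the one-year disease- and medication-free rule. The sleep disorder and its treatment must be exempt, or no patient would qualify.
2. Report how many of the 101 patients remain, and present the two comparisons side by side.
3. Judge consistency by the direction and size of the estimate with its interval, not by renewed significance. Where the estimates diverge, do not attribute the factor to sleep disorder.
4. State that the restriction leaves the low-exercise entry criterion, applied to patients only, untouched. Physical-activity differences cannot be called sleep-related on this basis.

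Study examinations says that medical history is collected by questionnaire and that a physician checks health history and medications, so no new measurement should be needed. The sponsor should confirm that the patients' records cover the full year.

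The cost is precision in the restricted analysis. If 20–40% of patients are set aside, 81 to 61 remain. The standard error against 107 reference men rises from 0.139 to √(1/107 + 1/81) = 0.147 or √(1/107 + 1/61) = 0.160, about 6% to 16%.
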